**Administrative Information**

***Trial Information***

Trial Number: NCT04805554

Trial Registry: ClinicalTrials.gov

Date of Registration: March 18, 2021

Contact: [name] [contact]

Funding: AHRQ Grant R21HS027037

Coordinating Center: Dell Medical School at the University of Texas Austin

Ethics Review: Initial approval by UT IRB on February 21, 2020 (#2018110042, modifications approved later)

Study Type: Interventional

Study Design: Randomized parallel assignment open label (unblinded) study

Sample Size: 200

Date of First Enrollment: February 22, 2021

Recruitment Status: Enrolling

Expected Completion: June 2022

Sponsor: The funder (AHRQ) has no role in study design, collection, management, analysis, or data interpretation. The funder has no role in the writing of the report or the decision to submit the report for publication.

Principal Investigators: [name]; [name]; [name]

Grant Holders: [name] and [name]

Protocol: Dell Medical School: [name] (KJB), [name] (LU), [name] (PJ), [name] (EL), [name] (ZT), [name] (KMK) [name] (PR). UT Health Science Center San Antonio: [name] (JT)

Roles: Clinical trial design / conception: PJ, JT, KJB, PR, KMK; Study initiation: PJ, JT, KJB, LU; Study implementation / operations: EL, ZT, KMK, KJB; Statistical analysis: PR; Study protocol and refinement: All authors; Synthesis of data analysis: All authors; Approval of final manuscript: All authors.

Data Management: PJ, [name]

Recruitment: EL, ZT

**Introduction**

***Background***

In the era of patient-centered care, there is a growing interest in educating and engaging patients in the clinical decision-making process. This sets patients and providers up for making the right treatment choices for a medical condition (Sepucha 2017)(duLong 2016)([name] 2013). Actively working through treatment options and using decision aids as incorporated into the clinical work flow is shown to generate positive attitudes amongst patients and providers during consultations (Williams 2017)(Mangla 2018)(duLong 2016).

The concept of shared decision-making utilizing decision aids has been advocated as a more patient-centered approach to orthopaedic surgical care (Mangla 2018)(duLong 2016)(Stacey 2014). Studies have demonstrated the positive impact of decision aids on patient knowledge, efficiency and quality of decision-making, treatment choice, and patient and surgeon experience in treatment of hip and knee OA ([name] 2013,Stacey 2014). The use of decision aids to generate dialogue and involve patients in the decision-making process may also enable more comprehensive discussions around all available treatment options. In this way, utilization of care may be increased in the management of joint pain secondary to osteoarthritis (Hofstede 2016). In association, the use of decision aids in routine orthopaedic care has shown reduced surgical rates, due perhaps to more informed discussions and decision-making (Sepucha 2017).

Decision aids may also contend with the influence of socioeconomic factors on treatment choices (Youm 2015). Those patients with less education and lower incomes are shown to be 1) less knowledgeable about their medical conditions and treatment options and 2) less able to arrive at a decision following consultations for joint pain related to osteoarthritis (Youm 2015). One study involving shared decision-making in the treatment of hip and knee osteoarthritis demonstrated the influence of the doctor-patient relationship on decision-conflict with a need for more information and clarity around the risks and benefits of surgery (duLong 2016).

This study evaluates a technology-enabled decision aid (OM1, Boston, MA, USA) that provides evidence-based education (i.e. on understanding the condition, treatment options and comparisons, patient values and question & answer quiz), preference assessment, and personalized, quantifiable benefit-risk ratio alongside the level of potential benefit in relation to joint stiffness, joint pain and quality of life. The study will be performed in the setting of an integrated care system providing patient-centered care for hip and knee OA over the full cycle of care.

The impact of a technology-enabled decision aid incorporating predictive analytics with machine learning capabilities on decision quality, activation, experience & functional outcomes of patients in this setting is relatively unknown. As a comparator or control group, this study will utilize identical evidence-based educational materials but will exclude the personalized risk ratio report and preference assessment.

***Objectives***

Assessing impact of a technology-enabled full decision aid (patient education, preference assessment, patient-specific predictive analytics) on decision quality, functional outcomes, concordance, shared decision making, patient/ provider satisfaction with consultation discussion, decisional conflict, and decision regret, consultation time, rates of surgical treatment compared to a control arm (patient education only).

***Trial Design***

This is a two-armed parallel group randomized controlled trial with an allocation ratio of 1:1 using block randomization that is testing the impact of a full technology-enabled decision aid (patient education, preference assessment, person-specific predictive analytics) compared to educational material only.

**Methods**

***Setting***

Subjects will be identified and recruited through the Lower Extremity Musculoskeletal Institute (MSKI) Clinic, an integrated practice unit at the University of Texas at Austin / Dell Medical School which is an urban, academic, tertiary care center. The subjects are identified as new patients presenting with knee pain with a presumptive diagnosis of OA and a scheduled appointment with KJB or KMK.

***Eligibility Criteria***

Inclusion Criteria (to be checked during huddle/ after check-in and x-ray/ at consent):

1. All new patients with a presumptive diagnosis of knee OA
2. Aged between 45 and 89
3. K-L grade of 3 or 4 (moderate to severe)
4. KOOS JR scores 0-85
5. Able to provide informed consent

Exclusion Criteria (to be checked during huddle/ after x-ray and check-in/ at consent):

1. Prior total knee replacement
2. Prior consultation with an orthopaedic surgeon for TKR
3. Prior experience with Joint Insights
4. Patients undergoing consideration for revision joint replacement
5. Patients seeking care for a trauma condition, or psoriatic/rheumatoid arthritis
6. Non-English or Non-Spanish speakers
7. Patients with BMI below 20 or above 46

***Interventions***

Intervention Arm: “Full Tool”

- Prior to consultation with a provider patients experience:
  - Demographic survey
  - Patient reported outcomes surveys:
    - PROMIS-Global 10
    - KOOS JR
  - OM1 Joint Insights educational module
  - OM1 Joint Insights preferences module
  - OM1 Joint Insights score report
- During consultation with a provider patients experience:
  - Discussion about the results of the decision aid
- Immediately after consultation with a provider patients experience:
  - Decision quality and satisfaction surveys:
    - DQI
    - CollaboRATE
    - DCS
    - Satisfaction score
- 3 and 6-9 months after consultation with a provider patients experience:
  - Decision quality surveys
    - DRS
  - Patient-reported outcomes surveys
    - KOOS JR
    - PROMIS-Global 10
  - *Patients may request to leave the study at any point without repercussion*
  - *Patients are contacted via phone, email, text, and/or Athena MyChart*
  - *Patients may participate in any concomitant care or interventions without limitation*
- 6-9 months after consultation with the provider and completion of all follow-up surveys:
  - Patients receive via mail or email a $25 gift card

Control Arm: “Education Only”

- Prior to consultation with a provider, patients experience:
  - OM1 Joint Insights educational module
- During consultation with a provider patients experience:
  - Standard care *without* discussion of the OM1 Joint Insights modules
- Immediately after consultation with a provider patients experience:
  - Decision quality and satisfaction surveys
- 3 and 6-9 months after consultation with a provider patients experience:
  - Decision quality surveys
  - Patient-reported outcomes surveys
  - *Patients may request to leave the study at any point without repercussion*
  - *Patients are contacted via phone, email, text, and/or Athena MyChart*
  - *Patients may participate in any concomitant care or interventions without limitation*

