***Sample Size***

The aim is to enroll a total of 200 subjects with randomization to either the intervention arm or the control arm of the study (100 controls and 100 interventions). The study is powered to account for 10% loss to follow-up, with a target sample size of 180 patients. We calculated the sample size for the RCT by treating the Decision Process score of the DQI as continuous. We aimed to detect a treatment effect size (i.e., Cohen’s D) as small as 0.5 (consistent with preliminary data from the first 26 subjects we have studied) with a type I error rate of 0.05 and power of 0.90, assuming equal sample size in intervention and control groups. Given our 8 randomization strata, we estimate a needed sample size of 180 participants, or 90 for each group. With an estimated loss-to-follow-up rate of 10%. Our target enrollment for the RCT is 200 participants, or 100 for each arm.

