***Recruitment Methods: Baseline Visit Questionnaires***

Patients from both randomization arms will be asked to complete the baseline surveys in REDCap at the end of their visit as soon as the consultation with their provider is complete:

- Patient Questions: Demographics
- Patient Questions: DQI
- Patient Questions: CollaboRATE
- Patient Questions: DCS10
- Patient Question: Satisfaction
- Patient-Facing Done Page (ask for patient preference of phone vs email for follow-up)

Researchers will then ask the relevant provider for the visit to complete the baseline survey in REDCap:

- Provider Question: Satisfaction

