***Study Methods: Follow-Up***

Emails from REDCap will be sent automatically at 3 and 6 months after the baseline visit. We will send up to 3 emails (approximately 7 days apart) with a link to complete follow-up PROMs. If there is not response by approximately 3 days after the third email, a researcher will call the patient up to 3 times to complete the follow-up surveys via telephone.

- Follow-Up Surveys to complete at 3 and 6 months
  - KOOS JR
  - PROMIS Global 10
  - DRS
- Time Windows
  - 3 month follow-up window: 2.75 to 4 months after baseline visit.
  - 6-9 month follow-up window: 5.75 to 10 months after baseline visit.
- For patients for whom Spanish is indicated as the preferred language, the research assistant will call using the interpreter service.
  - To call the interpreter service:
    - Dial [name]
    - Enter 1755794
    - Enter MSKI PIN: 1115
    - Select Language: Spanish
    - Connect & conduct follow-up questionnaires using interpreting service

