**Data Management & Analysis**

Data collection at baseline and follow-up will be conducted as above in “Methods” section.

Data management will be conducted using REDCap as detailed above. This is a confidential and secure database protected on UT servers.

Formal comparative analysis will follow the intent-to-treat principle. Primary analysis will compare the intervention and control groups by using multiple linear regression analysis. The model will include DQI score as the response variable and, as explanatory variables, a binary indicator for the intervention group and 7 binary indicator variables representing the 8 strata in order to reflect the stratified randomization design. Additionally, as a secondary analysis, we will compare treatment decisions between the intervention and control groups by using multiple logistic regression. The model will include the treatment decision as the binary response variable and the same explanatory variables as in the linear regression model. Depending on the uptake of the intervention, additional analyses will follow the “per-protocol” principle wherein the main treatment variable will be whether the Joint Insights tool was used.

For analysis of the 3- and 6-9 month data, we will fit linear mixed models for continuous outcomes35 and generalized estimating equations logistic regression models for binary outcomes36, including indicator variables for time point, for treatment group, and for the interaction between the two (yielding treatment effects at 3 months and at 6-9 months). Owing to the balanced design, it will be possible to fit an unstructured correlation model to eliminate any sensitivity to correlation model misspecification.

Data monitoring is not required for this study. No interim analysis is planned.

This is a minimal-risk study. Although we don’t anticipate any adverse events, any adverse events will be reported to the local IRB.

The datasets used and/or analyzed during the current study are available from the corresponding author on reasonable request.

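### The $25 gift card for completing follow-up is listed under the intervention arm only; as written, this risks arm-dependent non-response in the 3- and 6-9-month survey outcomes

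*Protocol*

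**What the plan says.** In the Protocol's Interventions section, the last timed item under the Full Tool arm is headed "6-9 months after consultation with the provider and completion of all follow-up surveys", and its single entry is "Patients receive via mail or email a $25 gift card".

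The Education Only list has the same 3- and 6-9-month survey block and the same three italic notes. It stops at the last of these, "Patients may participate in any concomitant care or interventions without limitation", with no gift-card item. The card is not mentioned in any other text shown.

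The surveys that earn the card are set out in Study Methods: Follow-Up, under "Follow-Up Surveys to complete at 3 and 6 months": KOOS JR, PROMIS Global 10 and the Decision Regret Scale (DRS). Data Management & Analysis handles them as follows: "For analysis of the 3- and 6-9 month data, we will fit linear mixed models for continuous outcomes". Binary outcomes get GEE logistic models, and both kinds of model have time, treatment and their interaction. Sample Size plans for one loss rate with no difference between arms: "With an estimated loss-to-follow-up rate of 10" per cent.

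**The concern.** A payment that depends on completing follow-up is meant to raise response. If it is offered in one arm only, response can differ by arm for a reason created by the trial's own procedures. The trial is unblinded, and patients are told their group at randomization.

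Three of the ten outcomes in the Outcomes table rest on these follow-up surveys: overall health (PROMIS Global 10), change in limitations (KOOS JR) and decision regret (DRS). Likelihood-based mixed models give valid comparisons when missingness depends only on observed data. They do not remove bias when non-response depends on the unobserved outcome. DRS is the most exposed: it is collected only at follow-up, so a patient who misses both contacts contributes nothing to it and has no earlier value to inform the model.

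**Working it through.** **1. Is the card really confined to one list?** The timed items of the two lists in Interventions compare as follows.

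| Timed item | Full Tool | Education Only |
|---|---|---|
| Before consultation | yes | yes (shortened) |
| During consultation | yes | yes |
| Immediately after | yes, instruments named | yes, not named |
| 3 and 6-9 months | yes, instruments named | yes, not named |
| Three italic notes | yes | yes, repeated |
| Gift card after all follow-up surveys | yes | **absent** |

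The card is the only timed item with no control counterpart.

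**2. Does other text fill the gap?** For the surveys, it does. Baseline Visit Questionnaires says "Patients from both randomization arms will be asked to complete the baseline surveys in REDCap at the end of their visit". Baseline Documentation records KOOS JR and PROMIS-10 without limiting them to an arm, and Study Methods: Follow-Up sets the follow-up surveys without an arm limit. For the card, nothing shown does so: the follow-up and follow-up documentation sections do not mention it.

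**3. Which outcomes are exposed?**
- Exposed: KOOS JR, PROMIS Global 10 and DRS at 3 and 6-9 months.
- Not exposed: the primary outcome ("The model will include DQI score as the response variable", collected at the end of the baseline visit), CollaboRATE, the Decisional Conflict Scale, satisfaction, consultation time, and knee replacement within 9 months, which is taken from Athena records.

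**4. The plan's own attrition figure.** Inputs from Sample Size: 180 evaluable, 10% loss, d = 0.5, alpha 0.05 (two-sided assumed, since sidedness is not stated).
- Enrolment: 180 / (1 - 0.10) = 200, as stated.
- Power at 90 per arm: SE = sqrt(1/90 + 1/90) = 0.149; 0.5/0.149 - 1.96 = 1.39; power = 0.918, in line with the stated 0.90.

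**5. Illustration of unequal loss.** The Protocol gives no arm-specific rate, so every loss difference and gap here is an assumption. Let g be the mean difference between responders and non-responders in SD units, the same in both arms. In an arm with loss L, the completer mean differs from the full-arm mean by L x g. The error in the arm difference therefore has size (control loss - intervention loss) x g. With 100 per arm and 10% loss in the paid arm:

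| Control loss | Completers | Power at d = 0.5 | Bias, g = 0.3 | Bias, g = 0.5 |
|---|---|---|---|---|
| 10% | 180 | 0.918 | 0 | 0 |
| 15% | 175 | 0.911 | 0.015 SD | 0.025 SD |
| 20% | 170 | 0.902 | 0.03 SD | 0.05 SD |
| 25% | 165 | 0.892 | 0.045 SD | 0.075 SD |
| 30% | 160 | 0.881 | 0.06 SD | 0.10 SD |

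A difference of 10 to 15 points with g of 0.3 to 0.5 gives 0.03 to 0.075 SD, which is 6% to 15% of d = 0.5. Over a wider grid (5 to 20 points, g from 0.25 to 1) the range is about 0.01 to 0.20 SD. Power changes little. The direction depends on whether responders do better or worse than non-responders, which is unknown. The formula describes a completer comparison; a mixed model could recover part of the bias where a missing value is predictable from an observed one.

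**The case against.** The strongest reply is that the control list is a shortened copy. It drops the instrument names, the demographic survey and the pre-visit KOOS JR and PROMIS, yet other sections show that controls complete these measures. Absence from that list therefore does not prove exclusion. Consent precedes randomization, and its script, which is not shown, may promise the card to everyone. The arm-specific randomization scripts mention no card for either group, and the follow-up procedure makes no distinction between arms. All of this stands. A reader might infer that controls are denied payment, but the Protocol does not establish that. What remains is that other sections restore the surveys to controls and none shown restores the card, so staff working from this text would pay one arm.

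A reader might also go further in four ways that the document does not support:
- **That differential attrition will occur.** It is a risk. The only loss rate given is a single 10%.
- **That the primary result is biased.** DQI is collected on the day of the visit, before any follow-up loss.
- **That controls would fall short of a planned 90.** That number was set for the DQI Decision Process score, not for the follow-up surveys.
- **That the reward itself distorts reported regret and function.** The card comes after all surveys are complete, so only its anticipation could act.

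**Conclusion.** The point holds in a limited form. The Protocol lists a completion-dependent reward under one arm of an unblinded trial, and nothing shown extends it to the other. Followed literally, it risks arm-dependent non-response in the 3- and 6-9-month KOOS JR, PROMIS Global 10 and DRS, and in nothing else. The size is unknown. The 0.03 to 0.075 SD figure rests on an assumed 10 to 15 point difference in loss, an assumed gap of 0.3 to 0.5 SD that is equal in both arms, and a completer comparison. That is small beside d = 0.5, which was itself chosen for a different outcome. If both arms are in fact offered the card, what remains is a one-line text correction.

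**What to change.** Move the gift-card item to a follow-up section common to both arms, or add it to the Education Only list with the same amount and trigger. Report completion of the 3- and 6-9-month surveys by arm.

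First establish what has been offered so far. If only one arm has been offered the card, offer it to controls from now on and disclose the difference when interpreting the follow-up outcomes. Paying controls retrospectively would not recover surveys already missed.

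The cost is one line of text and at most 100 x $25 = $2,500, or nothing further if both arms are already paid.

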***Allocation***

Sequence Generation: REDCap algorithm (see details below)

Concealment: Sequence concealed by REDCap algorithm

Implementation: Research Assistant (see protocol below for Randomization)

Blinding: Unblinded/ no masking

For the randomization, we will stratify by variables known or suspected to be predictive of decision quality and/or treatment choice by using stratified random block randomization. Participants will be stratified by 3 factors: ethnicity (Hispanic/non-Hispanic), insurance (public safety net insurance/other insurance) and attending surgeon. Block randomization will occur within each stratum with random block sizes of 4 and 6, and an equal number of patients assigned to the intervention and control arms within each block. These steps are carried out automatically in the REDCap study database. This strategy ensures that participants are equally distributed to treatment and control through time, therefore controlling for any time varying effects that may occur. The Dell Medical School Biomedical Data Science Hub will oversee the randomization.

***Outcomes***

This study will assess the impact of a technology-enabled decision aid on:

| **Outcome** | **Measure** |
| --- | --- |
| Decision quality | Knee Decision Quality Index Q3.1-3.5 |
| Concordance | Knee DQI Q1.6 & whether patient had TKA within 9 months (Athena) |
| Shared decision making | CollaboRATE survey |
| Patient/provider satisfaction with discussion | Satisfaction question |
| Consultation time | Duration of surgeon/patient consultation in minutes as measured by research assistant |
| Overall health | PROMIS Global 10 |
| Change in limitations | KOOS JR |
| Treatment selected | Treatment choice/arthroplasty rate |
| Decisional conflict | Decisional Conflict Scale 10 (low literacy) |
| Decision regret | Decision Regret Scale |

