    - *FULL TOOL:* “*This educational module should take about 5-10 minutes to read through, depending on your pace. When you are ready to move on to the next section, simply press “next” in the lower right-hand corner. When you reach the end of the education there will be a short quiz but do not worry, it is not graded. It is simply to help you test your own knowledge of what you learned. There will also be a few questions about your treatment preferences. Again, those are only for your benefit to help you think about the treatment options. There is no “right” answer. Finally, you will reach a set of survey questions identical to the ones you already answered in the lobby where you checked in. You may stop there, and I will fill out the survey using the information you have already given us. I will be back in 5-10 minutes and would be happy to answer any questions you have at that time.”*
    - *EDUCATION ONLY:* “*This educational module should take about 5-10 minutes to read through, depending on your pace. When you are ready to move on to the next section, simply press “next” in the lower right-hand corner. When you reach the end of the education there will be a short quiz but do not worry, it is not graded. It is simply to help you test your own knowledge of what you learned. I will be back in 5-10 minutes and would be happy to answer any questions you have at that time.”*
- Leave the room for 5-10 minutes
  - *Optional:* while patient is reading over the iPad materials, the RA completes the patient’s OM1 profile utilizing individual patient-reported outcome measure question responses to the KOOS, JR and PROMIS-10 Global as viewable in AthenaHealth.
  - The RA may also create a second module for patients reporting bilateral knee pain who are randomized to the full tool, so that the patient can get individualized scores for each side
- Return when time is up, and check if the patient has completed the educational module
  - If the patient is not done, politely offer more time
  - If the patient is done:
    - Close the tab with the educational module
    - *For education + preferences only patients:*
      - Thank them and leave the room
      - Inform the provider the patient is ready to be seen
    - *For full tool patients:*
      - Return to the OM1 enrollment tab and click “View Surgery Benefit & Risk Report”

[figure not shown]

- - - - This will open a new tab with the Joint Insights report

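### Concordance takes TKA within 9 months from Athena alone, and neither follow-up contact asks about knee replacement, so a TKA done elsewhere could be missed

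*Protocol*

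**What the plan says.** In the protocol's Outcomes table, concordance is measured by "Knee DQI Q1.6 & whether patient had TKA within 9 months (Athena"). A separate row, treatment selected, is measured by "Treatment choice/arthroplasty rate", with no data source and no time window.

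Recruitment is through one clinic, "an integrated practice unit at the University of Texas at Austin / Dell Medical School" (Setting). For both arms the Interventions section states: "Patients may participate in any concomitant care or interventions without limitation".

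Study Methods: Follow-Up lists KOOS JR, PROMIS Global 10 and the Decision Regret Scale under "Follow-Up Surveys to complete at 3 and 6 months", and gives a "6-9 month follow-up window: 5.75 to 10 months after baseline visit". Follow-Up Documentation leaves the surveys blank for patients lost to follow-up.

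Athena appears elsewhere as the record that study staff read, for example "KOOS, JR and PROMIS-10 Global as viewable in AthenaHealth" (OM1 Enrollment & Delivery). Data Management & Analysis plans a secondary logistic regression: "The model will include the treatment decision as the binary response variable".

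**The concern.** Concordance asks whether the patient's stated preference matched what was then done. It needs a correct answer on whether the knee was replaced. With one record system as the only source and no question to the patient, an outside TKA missing from that record looks the same as no TKA.

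The error works in both directions. A patient who wanted surgery and had it elsewhere would appear discordant. A patient who did not want surgery but had it elsewhere would appear concordant. Concordance and rates of surgical treatment are both stated objectives. The gap lies in data collection, so an analysis plan written later could define how unknown status is handled but could not recover answers never asked for.

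**Working it through.** **1. What the protocol fixes.**

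| Question | Protocol | Section |
| --- | --- | --- |
| TKA source for concordance | Athena, within 9 months | Outcomes |
| TKA source for arthroplasty rate | Not stated | Outcomes |
| Does Athena record surgery done elsewhere? | Not stated | – |
| Is other care restricted? | No, in either arm | Interventions |
| Do follow-up surveys ask about TKA? | No such item listed | Study Methods: Follow-Up |
| TKA status if lost to follow-up | No rule; surveys blank | Follow-Up Documentation |

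The ascertainment gap follows from these rows. Its size does not, because the protocol gives no TKA rate, no concordance rate and no share of TKAs done elsewhere. There is therefore no figure of the plan's own to reproduce on this point. The sample size of 200 rests on the DQI score.

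**2. Concordance (all inputs assumed).** Let *w* be the share preferring surgery, *t* the probability of TKA among them, *u* the probability of TKA among the rest, and *s* the share of TKAs that Athena captures. Assume no false entries and that an absent entry is read as no TKA. Then

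recorded concordance = *w·t·s* + (1 − *w*)(1 − *u·s*) = (1 − *w*) + *s*[*w·t* − (1 − *w*)*u*].

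| Assumed *w, t, u* | Formula | *s* = 1 | *s* = 0.9 | *s* = 0.8 |
| --- | --- | --- | --- | --- |
| 0.4, 0.7, 0.1 | 0.60 + 0.22*s* | 0.820 | 0.798 | 0.776 |
| 0.5, 0.6, 0.1 | 0.50 + 0.25*s* | 0.750 | 0.725 | 0.700 |

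For the comparison between arms:

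- Same true concordance in both arms (first row), capture 0.90 versus 0.80: spurious difference 0.22 × 0.10 = 0.022.
- Equal capture, same preference share in both arms: the true difference is multiplied by *s*, so it shrinks.
- Equal capture, different preference shares: the error need not shrink the difference. Take *w* = 0.5 versus 0.4, with *t* = 0.7 and *u* = 0.1 in both. True values are 0.80 and 0.82, a difference of −0.02. At *s* = 0.8 they become 0.50 + 0.8 × 0.30 = 0.740 and 0.776, a difference of −0.036.

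**3. Arthroplasty rate, only if it means surgery performed and comes from Athena (all inputs assumed).** Recorded difference = *s*₁*p*₁ − *s*₀*p*₀. With *p* = 40% versus 30%:

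- capture 0.9 in both arms: 36% − 27% = 9 points; odds ratio 1.56 becomes 1.52
- capture 0.8 in both arms: 32% − 24% = 8 points; odds ratio 1.49
- capture 0.9 versus 0.8: 36% − 24% = 12 points
- capture 0.8 versus 0.9: 32% − 27% = 5 points

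The standard error of the true difference at 100 per arm is √(0.4 × 0.6/100 + 0.3 × 0.7/100) = 6.7 points. Equal under-capture of this order is small beside sampling error. Unequal capture matters more: with 40% in both arms, capture of 0.9 versus 0.7 gives a spurious difference of 8 points and a rejection probability of about 0.23 at a two-sided 0.05.

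**4. Timing of a patient question.** The second contact may fall at 5.75 months, and its emails go out at 6 months. A question asked at 5.75 months leaves 9 − 5.75 = 3.25 months uncovered by self-report.

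**The case against.** The strongest reply is that the premise cannot be checked. The protocol does not say that Athena lacks outside operations, and it contains no rule coding an absent entry as no TKA. The permission for concomitant care concerns restrictions on treatment and does not mention place of care. The Background describes an integrated system covering the full cycle of care, and patients who had already consulted an orthopaedic surgeon about knee replacement are excluded, so outside TKAs may be few. All of this stands as a limit on size. It does not close the gap: the exclusion concerns consultations before enrolment, and nothing in the protocol confirms TKA status by a second route.

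A reader might infer that the arthroplasty rate is misclassified as well. The text does not support that as a statement. The Athena source and the 9-month limit belong to the concordance row only, and the treatment decision in the logistic model may be the choice made at the visit, which would not depend on where surgery took place.

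A reader might also infer that capture differs by arm. The open-label design, with a personalised report in one arm only, makes this conceivable, but no section gives evidence for it.

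Nor does the gap disturb the planned KOOS JR and PROMIS comparisons: they are between arms by intention to treat, and no planned model uses surgery status to explain those scores.

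Finally, a patient question has its own weaknesses: the second contact may come before month 9, and non-responders still depend on Athena alone.

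**Conclusion.** The point holds for concordance: as written, a TKA done elsewhere and not recorded in Athena is indistinguishable from no TKA, and concordance could be misclassified. For the arthroplasty rate it holds only if that outcome means surgery performed and is taken from the same source.

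The size cannot be computed from the documents. In the illustrations, recorded concordance falls by about 2 to 5 points at 80–90% capture. These figures rest on assumed preferences, TKA rates and capture, and on reading an absent entry as no TKA.

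The primary DQI analysis is unaffected, because the DQI is completed at the end of the baseline visit, and the sample size based on it is untouched. This is a cheap improvement to a non-primary outcome. It does not threaten the trial's main result.

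**What to change.** - Add one item to the existing 3- and 6-9-month REDCap form and phone script: knee replacement since the study visit, with which knee, date and place.
- Define TKA within 9 months as recorded in Athena or reported by the patient, for the knee already marked as primary under Baseline Documentation.
- State whether the arthroplasty rate means the choice at the visit or surgery performed. If surgery performed, use the same definition and window.
- For patients whose second contact falls before month 9, either rely on Athena for the remaining time and say so, or set that contact at or after month 9 within the existing 5.75-10-month window.
- Report the Athena-only definition as a sensitivity analysis, and report by arm how many patients have their status from Athena alone.

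The cost is one question at contacts already planned. Self-reported dates may be wrong. Ascertainment will be less complete in non-responders, which matters in an open-label trial and is why the count by arm is needed. Patients already enrolled may need one back-question. Moving the second contact to month 9 or later would also shift when the other surveys are completed.
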